### Follow-up assessment

#### 1-year follow-up

The patients will fill in the IIP–C, SCL–90-R, ARS and BDI. A blinded evaluator will interview the patient using the M.I.N.I. and SIDP–IV. The PFS and GAF will be scored by two blinded raters on the basis of an audiotaped interview. The DRS will be scored.

### Planned investigations

FEST–IT will be a randomized trial that compares short-term psychodynamic psychotherapy with and without transference interpretation to reduce relapse in adolescents with DSM-IV-defined MDD. The patients will be randomly allocated to STPP with or without transference interventions. This is a dismantling design in which a single component is added and/or varied to an existing treatment approach. The therapy is manualized. Outcomes will be assessed at planned follow-up points by outcome evaluators unaware of the treatment allocation. The therapists will be psychodynamically trained therapists who will undergo a 1-year training program succeeded by peer supervision in groups. This will help maintain the quality of the therapies. The therapies will be audiotaped to evaluate treatment adherence.

### Sample size and power

On the basis of standard posttest comparison of the two groups, 100 patients in this study will be enough to reveal a moderate effect size (0.55), with a significance level of 0.05 and a power of 0.80
[74]. In this study, an effect size (ES) of 0.55 equals 3.3 steps on the GAF scale, since the standard deviation across groups at posttreatment is 6. By using a pre-post treatment design, the power will increase. Adding data from 1-year follow-up will increase the power to detect differences even more. An α level of 0.10 has been decided on *a priori* for the moderator analyses and the subgroup analyses in this study to offset the risk of type II errors
[74].

### Statistical analysis plan

Intention-to-treat analysis will be performed. Characteristics of the treatment groups will be described at baseline. A linear mixed model will be used to analyze treatment effects of transference interventions in depressed adolescents. The statistical analyses will be performed with the linear mixed model using all data from all patients during the whole study period. Treatment response in FEST–IT will be the effect of transference intervention in depressed adolescents. The primary hypothesis will be explored by using this equation
[75]:

Outcome measure = intercept + time + time × treatment + QOR + time × treatment × QOR + residuals.

Both predictors and moderators are pretreatment variables that might affect the strength or direction of the treatment response. Predictors do so regardless of treatment condition. Moderators
[76] differentially influence outcome, however, depending on treatment condition
[77,78]. Moderators specified in advance are QOR, Personality Disorder, and gender. Those patient variables will be explored as predictors or moderators of outcome.

To explore the effects of moderators in FEST–IT, the following model will be used
[75]:

Outcome measure = intercept + time + time × treatment + QOR + time × treatment × QOR + residuals.

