### Related studies

#### First Experimental Study of Transference–Interpretations

The First Experimental Study of Transference–Interpretations (FEST)
[27] is a RCT designed to explore specific long-term effects of transference work in time-limited dynamic psychotherapy in adults. Regular patients from general practice, private specialist practices and psychiatric outpatient departments were referred to the study therapists and assessed for eligibility. Inclusion criteria were liberal. One hundred patients were randomized to two different dynamic psychotherapies. Both treatments used general psychodynamic principles. One treatment avoided an interpretive focus on the ongoing patient–therapist interaction (comparison group). The other treatment used material from the patient–therapist interaction as the most important vehicle for clarifications, confrontations and interpretations (transference group).

In FEST, no significant differences between the two groups with regard to baseline characteristics could be detected. Treatment integrity was excellent
[26]. Only use of transference work was significantly different between the two treatments. The two primary outcome measures were the Psychodynamic Functioning Scales (PFS) (clinician-rated)
[25,26,50,51] and the Inventory of Interpersonal Problems (IIP–C)
[52]. The two secondary outcome measures were the Global Assessment of Functioning Scale (GAS) and the Symptom Checklist-90-R (SCL-90)
[53].

The Quality of Object Relation Scale (QOR), a measure of difficulties in relational functioning
[54], was an important moderator of the effect of transference interventions
[26,27]. Patients with the most problematic relationships with other people profited most from dynamic psychotherapy with transference interventions. Gender was also found to be a moderator
[32,33]: Women experienced a significantly better treatment effect of transference work than men.

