### Aims

The primary hypothesis is that the transference group will have a more favorable course than the comparison group over time (that is, a significant improvement on the Psychodynamic Functioning Scales (PFS) and Inventory of Interpersonal Problems–Circumplex Version (IIP-C) and the measured depression by Mini International Neuropsychiatric Interview (M.I.N.I.), Beck Depression Inventory (BDI) and Montgomery Åsberg Rating Scale (MADRS) during the whole study period). The second hypothesis is that patients with a history of low QOR scale score and/or lacking personality disorders benefit more from therapy with transference work than from therapy without it. The third hypothesis is that female adolescents have better treatment effect of transference work than male adolescents do.

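### One equation serves both the primary hypothesis and the moderator analysis: its time × treatment term is the average effect only if QOR is centred, and it omits time × QOR

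*Protocol article*

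**What the plan says.** Under Aims, the primary hypothesis is an unconditional comparison of the arms: "the transference group will have a more favorable course than the comparison group over time". Moderation is a separate, second hypothesis, that "patients with a history of low QOR scale score and/or lacking personality disorders benefit more from therapy with transference work".

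The Statistical analysis plan section then says "The primary hypothesis will be explored by using this equation" and prints:

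"Outcome measure = intercept + time + time × treatment + QOR + time × treatment × QOR + residuals"

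A few lines later it turns to moderators with "To explore the effects of moderators in FEST–IT, the following model will be used" and prints the same equation again, term for term.

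The Sample size and power section uses a significance level of 0.05 for the main comparison and 0.10 for the moderator and subgroup analyses. The article therefore treats these as two different analyses. It does not say that QOR is centred, which coefficient or contrast tests the primary hypothesis, or how QOR is distributed.

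**The concern.** In a model with a three-way interaction, the lower-order time × treatment term has meaning only at the zero point of the moderator. If QOR enters on its raw scale, that term is the arm difference in slope for a patient with QOR = 0, which is not what the primary hypothesis asks. The difference would vanish if there were no moderation, but the plan cannot count on that. Its second hypothesis predicts moderation, and the article says of the adult study being replicated that QOR "was an important moderator of the effect of transference interventions".

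The equation also has no time × QOR term. An ordinary prognostic relation between QOR and change, equal in both arms, then has nowhere to go except the treatment terms. The same section says that the patient variables will be explored as predictors or as moderators, and this model cannot tell the two apart.

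At stake are what the primary test estimates, and whether a significant moderator term can be read as moderation.

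**Working it through.** **1. The plan's own figure.** Inputs from Sample size and power: 100 patients (50 per arm), effect size 0.55, alpha 0.05 (two-sided assumed, since the article does not say). SE = √(2/50) = 0.20 SD. Power = Φ(0.55/0.20 − 1.96) = Φ(0.79) = 0.785, which agrees with the stated 0.80 to within two points. Also 0.55 × 6 = 3.3 GAF steps, as stated.

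**2. What the coefficients mean.** Call the time × treatment coefficient b2 and the time × treatment × QOR coefficient b3.
- Arm difference in slope at QOR = q: b2 + b3·q.
- At q = 0 this is b2. Averaged over patients it is b2 + b3 × mean(QOR).
- The two agree only if b3 = 0 or QOR is centred at its mean.

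**3. Precision of raw b2.** Assumption: QOR mean/SD = r, with r = 2, 3 or 5. Take one change score per patient with SD 1. The comparison arm contributes variance 1/50. The transference arm, extrapolated to QOR = 0, contributes (1 + r²)/50. So SE(b2) = 0.20 × √((2 + r²)/2).

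| r | SE(b2) | Power at 0.55, raw b2 |
|---|---|---|
| 2 | 0.20 × 1.732 = 0.346 | 0.355 |
| 3 | 0.20 × 2.345 = 0.469 | 0.216 |
| 5 | 0.20 × 3.674 = 0.735 | 0.116 |

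Power here is Φ(0.55/SE − 1.96) + Φ(−0.55/SE − 1.96), against 0.785 with time + time × treatment alone. Simulating two visits with pre-post correlation 0.5 gives 0.42, 0.23 and 0.13, against 0.89.

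**4. False rejection by raw b2 when QOR only predicts change.** Assume no treatment effect and a prognostic effect of 0.2 SD per SD in both arms. With no time × QOR term, the expected value of b2 is −0.2r, that is −0.4, −0.6 and −1.0. Set against the standard errors in step 3, simulated rejection at 0.05 is 21–25% (change score) and 19–25% (two visits).

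**5. Raw b2 when QOR moderates around a zero average effect.** With moderation of 0.3 SD per SD, b2 is 0.3r in absolute size: 0.6, 0.9 and 1.5 SD. In the two-visit simulation it is significant in 46–59% of trials.

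**6. The same equation, evaluated at the mean.** Testing b2 + b3 × mean(QOR), or centring QOR, restores the primary test. Power is 0.77–0.78 (change score) or about 0.89 (two visits), and rejection is about 4–6% in the settings of steps 4 and 5.

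**7. The moderator term, with QOR centred.** Assume no moderation and the same prognostic effect of 0.2. As printed, b3 is simply the QOR slope in the transference arm. Its expectation is 0.2 and its SE is 1/√50 = 0.141, so z = 1.414. At alpha 0.10, rejection = Φ(1.414 − 1.645) + Φ(−1.414 − 1.645) ≈ 0.41. Simulation gives 38–42% (change score) and 35–37% (two visits). With time × QOR added, rejection returns to about 10%.

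**The case against.** A reader might infer that the trial, followed as written, has no test of its primary hypothesis. The article does not support that. It specifies a model but names no coefficient as the test. Step 6 shows that the printed equation, even with raw QOR, holds a valid overall contrast with essentially the power of the simpler model. The losses in steps 3 to 5 arise only if someone tests the raw coefficient.

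It can also be said that centring and choice of contrast are details that an article commonly leaves to a full analysis plan, and that the first equation looks like the moderator equation pasted in by mistake, since Aims and the two alpha levels keep the questions apart. Both are fair, and the second is plausible. Neither removes the point. The objection is to an explicit equation that the article assigns to the primary hypothesis and that is identical to the moderator model, so the text needs correcting whatever the cause. As printed, it leaves open an effect at QOR = 0, an effect at mean QOR, or a model without QOR.

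The sizes are conditional. The article gives no QOR mean, SD or prognostic strength, so the figures illustrate what could happen and do not forecast this trial's performance.

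Centring is no answer to the missing time × QOR term. It makes that omission harmless for the primary term and leaves the moderator test misleading.

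**Conclusion.** The point holds in two parts.

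- **Primary hypothesis.** The printed model is the moderator model. Its time × treatment coefficient is the average effect only under mean-centring, or through a contrast at mean QOR, and the article states neither. If the raw coefficient were tested, power at 0.55 would drop from about 0.8–0.9 to about 0.1–0.4, and false rejection would be about 20–25% when QOR merely predicts change.
- **Moderator hypothesis.** Without time × QOR, a purely prognostic QOR yields a significant moderator term in about 35–42% of trials at alpha 0.10, with QOR centred and no moderation present.

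The figures assume 50 per arm and a prognostic effect of 0.2 SD per SD. Those for the raw primary coefficient also assume a QOR mean/SD of 2 to 5. The algebra needs none of these assumptions. The conclusion is that the primary test is left ambiguous and the moderator model is mis-specified. It is not that an overall test is impossible.

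**What to change.** 1. Give the primary hypothesis its own model: intercept + time + time × treatment + patient random effects + residual. QOR may enter at most as a mean-centred baseline covariate. Name time × treatment as the test, at alpha 0.05.
2. For the moderator hypotheses, at alpha 0.10, use the three-way model with the moderator mean-centred and time × moderator added: time × QOR, and likewise for personality disorder and gender. The time × moderator term then carries prediction and the three-way term carries moderation.

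The cost is a line or two of wording and one extra term per moderator model, with no new data. The extra term widens the standard error of the moderator coefficient from 1/√50 = 0.141 to √(2/50) = 0.20 SD per SD. The smaller figure relies on QOR having no effect on change in the comparison arm.

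### The moderator model omits time × QOR, so it cannot separate a predictor from a moderator and, under common treatment codings, can often mistake one for the other

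*Protocol article*

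**What the plan says.** All of this is in the protocol article. Under Statistical analysis plan, the moderator equation is introduced with "To explore the effects of moderators in FEST–IT, the following model will be used" and reads "Outcome measure = intercept + time + time × treatment + QOR + time × treatment × QOR + residuals". The identical equation is printed earlier in that section for the primary hypothesis.

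The section also defines its terms. Of predictors it says "Predictors do so regardless of treatment condition"; moderators, by contrast, "differentially influence outcome, however, depending on treatment condition". QOR, personality disorder (PD) and gender are named in advance, and "Those patient variables will be explored as predictors or moderators of outcome".

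Under Sample size and power, the threshold for the moderator and subgroup analyses is set: "An α level of 0.10 has been decided on" in advance. The article does not say how treatment is coded or whether QOR is centred.

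**The concern.** In a model of change over time, a variable that affects response alike in both arms acts through time × variable. The main effect of QOR only shifts the level of the outcome at every visit. The printed equation therefore has no place for the predictor effect that the section wants to distinguish from moderation.

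What happens to such an effect depends on the coding of treatment:

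- **0/1 coding.** Change in the comparison arm is forced to be unrelated to QOR. Most of a general QOR effect on change then falls on time × treatment × QOR.
- **Factor with both arm levels.** The three-way term holds one QOR slope per arm. Its joint test asks whether QOR predicts change in either arm, which is not a test of moderation.

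The second and third hypotheses (for whom transference work helps) rest on this term. A finding that patients with certain QOR scores change more in any therapy could be reported as evidence about transference work.

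**Working it through.** **The plan's own figure.** The article gives no operating figure for the moderator test beyond its alpha. Its one power statement, "with a significance level of 0.05 and a power of 0.80" for 100 patients and an effect size of 0.55, is roughly reproduced with 50 per arm, two-sided: 0.55 × √(50/2) = 2.75, and Φ(2.75 − 1.96) = 0.785. I therefore use 50 per arm.

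**Inputs.** From the article: the equation, 100 patients, alpha 0.10. Assumed because the article gives none: two visits, unit variance, correlation 0.5, moderator centred with SD 1, linear time, no true moderation, and a predictor effect g (SD of change per SD of moderator, equal in both arms) of 0.1 to 0.4.

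**Closed form, 0/1 coding, printed equation.** Let b be the QOR main effect and γ the three-way coefficient.

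1. The inverse of the visit covariance matrix is (1/0.75) × [1, −0.5; −0.5, 1].
2. Information, summed over arms: I(bb) = 100 × 1.3333 = 133.33; I(bγ) = 50 × 0.6667 = 33.33; I(γγ) = 50 × 1.3333 = 66.67. Determinant: 133.33 × 66.67 − 33.33² = 7,778.
3. SE(γ) = √(133.33 / 7,778) = 0.131.
4. A pure predictor effect g contributes 66.67g to the score for b and 66.67g to the score for γ. Hence E(γ) = 66.67g × (133.33 − 33.33) / 7,778 = 0.857g. About 86% of the predictor effect is booked as moderation.
5. With z = 0.857g / 0.131, the rejection rate is Φ(z − 1.645) + Φ(−z − 1.645).

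| g | z | Closed form | Simulated, printed equation | Simulated, time × QOR added |
|---|---|---|---|---|
| 0.1 | 0.65 | 17% | 17.2% | 10.1% |
| 0.2 | 1.31 | 37% | 36.7% | 10.4% |
| 0.3 | 1.96 | 63% | 60.2% | 9.6% |
| 0.4 | 2.62 | 83% | 80.6% | 9.1% |

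The simulations used 2,000 trials per setting. They fall a little below the closed form at larger g, as expected if the misfit inflates the estimated residual variance, which the closed form takes as known.

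**Three visits.** A REML mixed model (assumed random-intercept SD 0.7, residual SD 0.7, baseline QOR effect 0.3), with g in outcome units over follow-up per SD of moderator, at g = 0.1, 0.2, 0.3 and 0.5:

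- 0/1 coding, printed equation: 19%, 38%, 61% and 90%. With time × QOR added: 10% to 13%.
- Factor coding, joint two-degree-of-freedom test: 22%, 55%, 85% and 99%. The contrast between the two arm slopes from the same fit stays at 10% to 13%.
- ±0.5 coding, balanced arms, printed equation: 9% to 14%, with a mean three-way coefficient near zero.
- At N = 400 and g = 0.2, the 0/1 rate is 85%. A larger trial does not cure it.

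**Binary moderator.** With an even split, 0/1 coding and two visits, between-group differences in change of 0.1, 0.2, 0.3 and 0.4 SD give 12%, 16%, 25% and 36%. An even binary variable has SD 0.5, so a difference of 0.4 corresponds to g = 0.2, for which the table shows 37%.

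**The case against.** **Coding.** The article fixes none. With ±0.5 coding and near-balanced arms, which the planned two-and-two allocation within therapist makes likely, the printed equation roughly keeps its nominal error rate. This stands, and it rules out an unconditional claim. It does not remove the defect: 0/1 and factor coding are common, nothing in the article excludes them, and under ±0.5 coding the predictor effect still has no term.

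**Gender.** The Background reports that earlier work did not show gender to be a general predictor of psychotherapy outcome. If that holds here, the gender model keeps its 10% rate. This also stands. The same Background says that personality traits influence the effect of psychotherapy, so the concern is better supported for QOR and PD.

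**Shorthand.** The equation shows no random effects, writes out only QOR, and may be a condensed form, with a separate predictor model in an analysis plan not shown here. This carries limited weight. The fixed effects are printed in full, twice, and a separate predictor model would not repair the three-way test in this one.

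**Power.** Adding the term widens the standard error, and the authors chose alpha 0.10 to guard against type II error. That is a real cost. Part of the power given up, however, came from assuming that QOR has no effect on change in the comparison arm.

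**Conclusion.** The concern holds in conditional form. The printed equation cannot make the distinction that its own section sets out. Under 0/1 coding at alpha 0.10, a continuous variable with no moderating effect would be declared a moderator in about 17% to 80% of trials for assumed predictor effects of 0.1 to 0.4 SD per SD. Factor coding with a joint test has the same fault. The sizes rest on assumed predictor effects, correlation and linear time; the article supplies none of these.

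Three stronger readings are tempting but not supported:

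- That a mere predictor *will* be declared a moderator. The rate depends on the coding and on the size of the effect. Even under 0/1 coding, most trials with g of 0.1 or 0.2 would not do so.
- That the 80% figure applies to gender or PD. It is for a continuous moderator; a binary one gives lower rates at the same between-group difference.
- That the primary treatment comparison is shown to be biased because it shares the equation. That would turn on how QOR is scaled, which the article does not state. The demonstrated consequence is for the moderator analyses.

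**What to change.** For each moderator M (QOR, PD, gender), fit a separate model:

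Outcome = intercept + time + M + time × M + time × treatment + time × treatment × M + random effects + residuals.

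Centre M and state the treatment coding. Read time × M as the predictor effect: the effect in the comparison arm under 0/1 coding, the average over arms under ±0.5 coding. Test time × treatment × M at the planned alpha, conditional on time × M. If treatment is entered as a factor, test the difference between the two arm slopes, not the joint term. Fix this before outcome data are seen by arm.

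The cost is one extra fixed effect per model with linear time (more if time is categorical) and no new data. Precision falls. In the two-visit setting under 0/1 coding with no general QOR effect, the simulated standard error of the three-way term rises from 0.134 to 0.178 (closed form: 0.131 to √(2 × 0.75 / 50) = 0.173). Power for a true moderation of 0.4 drops from about 91% to 72%. The plan should disclose this trade-off.

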[46]. In a randomized controlled study, the included patients are randomized to a study treatment condition or to a different treatment condition or placebo. The response in a treatment group is compared to the response in a control condition. The efficacy of a treatment might thus be determined. Patients and evaluators should be blinded to treatment group. Efficacy studies emphasize the internal validity by (1) controlling the types of patients included in the study, (2) using manuals to standardize the treatment, (3) training the therapists prior to the study, (4) supervising the therapists during treatment, (5) monitoring the technique adherence and the “dose” of the therapy, (6) assigning participants randomly to treatments, and (7) selecting the primary outcome measures before the study begins
[47].

Borkovec and Sibrava
[48] stated that even the RCT method applied in psychotherapy research might ignore what specific therapist behavior causes the change in the patient during and after therapy. They maintained that psychotherapy studies mostly compare therapy modes that differ in a number of ways. Therefore, RCTs often do not generate significant basic knowledge.

Borkovec and Sibrava’s advice is to focus on identification of putative specific techniques that cause patient improvement. Studies should investigate treatment conditions that differ in only one component. Dismantling or component control designs contrast the complete therapy (for example, dynamic psychotherapy with transference interventions) with the same therapy with experimentally manipulated differences solely in one dimension (for example, dynamic psychotherapy without transference interventions). If the patient expectations and the quality of the patient–therapist relationship in both conditions are equal, therapist effects are minimized, and the quality with which interventions are given is equal in both groups, then the study offers the best possibility of detecting causal relationships between the specific technique and outcome.

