Each therapist will treat at least four patients with psychodynamic psychotherapy: two patients with and two patients without transference interventions. Thus, the randomization will be stratified. The order in which each therapist’s patients are allocated to each therapy mode will be drawn by one of the main researchers, a coordinator who will stay in direct contact with the therapist. To minimize bias that could arise from knowledge of treatment allocation, the following strategies will be employed: (1) The interviewers will be blinded to treatment allocation, (2) evaluators and therapists will not communicate with each other about the patient after inclusion, and (3) all evaluation and assessor interviews will be audiotaped and rerated by independent raters, who will be blinded to the randomization. If blindness is broken and the evaluator knows the randomization for one patient, all subsequent assessments will be carried out by an alternative evaluator
[49]. Adherence to the randomization will be evaluated by blind raters by listening to three to five of the audio taped sessions from each patient and scoring them on the Specific Transference Technique Scales
[27].

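### Randomization is stratified by therapist, but the printed analysis model has no therapist term, so the standard error of the treatment effect may be off in either direction

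*Protocol article*

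**What the plan says.** Under Randomization procedures and methods used to minimize bias, the protocol article states: "Each therapist will treat at least four patients with psychodynamic psychotherapy", two with and two without transference interventions. It continues: "Thus, the randomization will be stratified". The order in which a therapist's patients go to the two modes is drawn separately for each therapist. Therapist is therefore the stratification factor and is crossed with treatment. With 100 patients there can be at most 100 / 4 = 25 therapists.

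Under Statistical analysis plan, the article announces a linear mixed model and prints one equation twice, for the primary hypothesis and again for the moderators: "Outcome measure = intercept + time + time × treatment + QOR + time × treatment × QOR + residuals". Therapist is not mentioned in that section. Under Sample size and power, the calculation is a plain two-group post-test comparison "with a significance level of 0.05 and a power of 0.80", without clustering.

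In the Background, a general and conditional sentence about dismantling designs counts it among the conditions for causal inference that "therapist effects are minimized". That sentence does not describe this trial's analysis.

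**The concern.** A factor used to restrict the randomization would normally appear in the analysis. Here it is in the design and absent from the written model. Two consequences pull in opposite directions.

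- **Therapist differences common to both arms.** Balanced allocation removes these from the treatment comparison, but a model without therapist leaves them in the error. The reported standard error is then too large.
- **Therapist differences in the treatment effect.** Some therapists may deliver one mode better than the other. This adds real variation to the treatment contrast, which a model treating patients as independent does not count. The reported standard error is then too small.

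The trial aims to isolate one technique that the same therapists both deliver and withhold. The second kind of variation bears directly on that aim, and the printed model neither shows it nor allows for it.

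**Working it through.** **Inputs from the article.** N = 100, taken as 50 per arm; α = 0.05, taken as two-sided; effect size 0.55, since "an effect size (ES) of 0.55 equals 3.3 steps on the GAF scale", "since the standard deviation across groups at posttreatment is 6"; at least 2 + 2 patients per therapist.

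**Assumptions.** The article gives no therapist variance. I take a therapist share *a* of 0.05 to 0.20 and a therapist × treatment share *w* of 0.05 to 0.10 of total variance. Unless stated otherwise there are K = 25 therapists with exactly four patients each and no dropout.

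**1. The article's own power.** SE = 6 × √(2/50) = 1.20. Power = Φ(3.3/1.20 − 1.96) = Φ(0.79) = 0.785. This agrees with the stated 0.80 within 2 points.

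**2. Therapist main effect only (post-test comparison).** Allocation is balanced within therapist, so the true SE is 6 × √(2(1 − a)/50). A test without therapist uses the pooled within-arm variance, expected at 36 × (1 − a/49), so its SE stays near 1.20. Type I error = 2Φ(−1.96 × model SE / true SE).

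| a | True SE | Model SE | Ratio | Type I | Power without term | Power with term |
|---|---|---|---|---|---|---|
| 0.05 | 1.170 | 1.199 | 1.025 | 0.044 | 0.791 | 0.806 |
| 0.10 | 1.138 | 1.199 | 1.053 | 0.039 | 0.798 | 0.826 |
| 0.20 | 1.073 | 1.198 | 1.116 | 0.029 | 0.813 | 0.867 |

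Holding the SD at exactly 6, the last type I error is 0.028. The power given up is 1.5, 2.8 and 5.4 points.

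**3. Therapist × treatment variation only.** In SD units the true variance is 2(1 − w)/50 + 2w/K, against 2/50 = 0.040 in the model.

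- w = 0.05, K = 25: 0.038 + 0.004 = 0.042; type I error 0.056.
- w = 0.10, K = 25: 0.036 + 0.008 = 0.044; type I error 0.062.
- w = 0.10, K = 12.5 (eight patients each): 0.036 + 0.016 = 0.052; type I error 0.086.
- w = 0.10, K = 8: 0.036 + 0.025 = 0.061; type I error 0.112.

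**4. Both together, K = 25.** With a = w = 0.05 the variance is 2(0.90)/50 + 2(0.05)/25 = 0.036 + 0.004 = 0.040, the same as the model's. Type I error is 0.050. Equal shares of 0.10 give the same result.

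**5. The effect the printed model tests.** Steps 2 to 4 concern a post-test difference, whereas the equation tests time × treatment. A simulation of patient slopes (20,000 runs per case, 25 therapists with 2 + 2 patients; simulation error of type I about 0.0015) gave:

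- constant therapist intercept, variance 0.2: SE ratio 1.00, type I error 0.051;
- therapist slope share 0.10: ratio 1.04, type I error 0.040;
- therapist slope share 0.20: ratio 1.09, type I error 0.033;
- therapist × treatment slope share 0.05: ratio 0.97, type I error 0.056;
- both slope shares 0.05: ratio 1.00, type I error 0.050 without therapist and 0.057 with an additive therapist effect only.

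The last line shows that removing the common therapist variation also removes the offset, so variation in the treatment effect has to be examined alongside it.

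**The case against.** The strongest objection is that the equation lists no random effects at all, not even one for patient. A mixed model of repeated measures needs some within-patient covariance, so the printed line may show only the fixed part, and an analysis plan not shown may supply the rest. This stands as a limit on what can be known: the article does not prove that the fitted model will ignore therapist. It does not remove the mismatch, because the article writes the model out for both analyses and leaves out the factor it randomizes by.

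A reader might infer that the standard errors are wrong, or that false positives are inflated. The article supports neither. With therapists crossed 1:1 with arm, an omitted common therapist effect makes the test conservative. Inflation requires treatment effects that vary by therapist, and equal shares of both cancel at four patients per therapist. A constant therapist intercept has no effect on time × treatment.

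Nor is the benefit of stratification thrown away. Balance lowers the true variance of the estimate whether or not therapist is modelled; only the reported precision suffers. The largest inflation figures need 8 to 13 therapists and no common therapist effect, while the article fixes only a minimum caseload.

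Estimability is also a fair point. With two patients per therapist and arm, a balanced analysis of patient slopes (F on 24 and 50 degrees of freedom) puts the therapist × treatment variance at or below zero in about 41% of trials at a share of 0.05 and about 30% at 0.10. Requiring that term in every model would be too much.

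**Conclusion.** The point holds as a mismatch between the design and the stated analysis. Therapist governs the allocation and is absent from the only model the article gives. The direction of the resulting error cannot be determined from the document. With 25 therapists the size is modest: the standard error is roughly 2.5% to 12% too large for common therapist shares of 0.05 to 0.20, or 2.5% to 5% too small for therapist × treatment shares of 0.05 to 0.10. Larger caseloads make the second case worse. All of this rests on assumed variance shares, equal caseloads and no dropout. The percentages are for a post-test comparison; the slope simulation shows the same directions. The change is worth making because it costs little, not because the planned test has been shown to be invalid.

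**What to change.** In the Statistical analysis plan section, state that therapist, as the stratification factor, enters the mixed models for the primary and the moderator analyses as a random intercept and a random slope on time, with small-sample degrees of freedom (Kenward-Roger or Satterthwaite). Write out the patient-level random or covariance structure at the same time, so that the equation is complete.

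Prespecify a sensitivity analysis that adds therapist × treatment variation on time. Give the order in which random terms are dropped if a variance is estimated at zero or the model does not converge.

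The cost is a change of wording and slightly more analysis work. Therapist identity is already known from the allocation, and no patient procedure changes. The random part may have to be simplified, and with two patients per therapist and arm this will not be rare for the therapist × treatment term.
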